### 2 Study design

We will conduct a randomised partially-blinded controlled 2#215;2 factorial trial. First, adults admitted to the ICU at the Hospital for Tropical Diseases will be randomized to receive either human (3000 IU) or equine (21,000 units) intramuscular antitoxin. Second, participants will be randomized to receive either standard treatment with intramuscular antitoxin alone or with the addition of 500 IU intrathecal human antitoxin. Patients with contra-indications to lumbar puncture or antitoxin treatment will be excluded. Patients who have already received a treatment dose of intramuscular antitoxin will have the intramuscular injection omitted.

All patients will receive other standard tetanus treatment as deemed necessary by the attending physicians. Spasms will be treated with benzodiazepines as first-line therapy. Patients with spasms not controlled with benzodiazepines will receive tracheostomy, paralysis, magnesium sulphate and mechanical ventilation. Heart rate, blood pressure, respiratory rate, temperature, oxygen saturation and daily drug use will be recorded throughout the ICU stay. Patients will be followed following discharge from hospital until 240 days for disability/ death.

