***2.2 Secondary End Points***

•Duration of ICU stay•Duration of hospital stay•Duration of mechanical ventilation•In hospital and 240-day mortality and disability•New antibiotic prescription during ICU stay (excluding antibiotics for tetanus or initial entry site infection)•Incidence of Ventilator Associated Pneumonia•Incidence of the clinical syndrome of autonomic nervous system dysfunction•Total dose of benzodiazepines and pipecuronium during hospital stay•Incidence of adverse events

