The primary outcome measure, requirement for mechanical ventilation during ICU stay, will be summarized as x/n (%) in each group and compared between the groups based on a logistic regression model with the two interventions (intrathecal treatment vs. sham procedure, human vs equine intramuscular treatment) as the only covariates without an interaction term. The main comparison is the comparison between intrathecal treatment vs. sham procedure, but the effect of the second randomized intervention will also be summarized as a secondary comparison. As odds ratios from logistic regression are somewhat difficult to interpret for a clinical audience, we will additionally summarize relative risk reductions between the groups based on a binary regression model with a log-link rather than the logit link function used in logistic regression. Interactions between the two interventions are not expected and interaction tests will have low power but we will nevertheless assess potential interactions informally through interaction plots and formally through a likelihood ratio test for an interaction in the logistic regression model. Should the interaction test reach formal significance, we will also perform pair-wise comparisons between the 4 treatment arms.

Potential heterogeneity of the treatment effect will be assessed based on appropriate interaction (likelihood ratio) tests and the following pre-defined sub-grouping variables:

•The Tetanus Severity Score
^27^ (calculated based on information available prior to randomization only) stratified according to tertiles of the observed TSS.•Age: (≤70, 71-80, >80 years)•Pre-existing medical conditions: moderate severe illness, severe illness defined according to ASA physical state scale•Anti-toxin prior to admission

In addition, the primary endpoint will be modelled using a logistic regression model including the two interventions plus additional adjustment for the Tetanus Severity Score, age and pre-existing medical conditions.

Duration of hospital stay, duration of ICU stay, and 240 day mortality will be visualized using Kaplan-Meier curves for all 4 study arms and, additionally, for all patients with and without intrathecal treatment. Formal comparisons of these outcomes (and in-hospital mortality) will be based on Cox regression models with the two interventions as the only covariates using a similar analysis strategy as for the primary outcome described above. 

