Other binary endpoints will be analysed in the same way as for the primary outcome. In addition, the rate of new antibiotics prescriptions, ventilator associated pneumonia and other predefined HAI, and the clinical syndrome of autonomic nervous system dysfunction will be modelled with a Poisson-regression model with the log-transformed duration of ICU stay included as an offset.

The cost–effectiveness analysis will be performed from the healthcare provider perspective, thus including direct costs resulting from the implementation of the intervention in the ICU and subsequent costs during the hospital stay, as well as any costs associated with re-admission during the 240 day follow-up. This will include the costs for standard tetanus treatment, the incremental cost of intrathecal human antitoxin administration, and those for any other diagnostics and treatments provided during ICU admission, including time spent on mechanical ventilation.

Prospectively collected data entered in the Case Report Forms from all patients included in the trial will be used for the cost analyses. The unit costs of intrathecal human antitoxin administration and those for mechanical ventilation will be estimated using a detailed micro costing approach. The cost per day of mechanical ventilation will account for the annualized cost of the equipment, maintenance, consumables and staff time.

If the intervention does improve patient survival at a higher cost, we will calculate the incremental cost per ICU survivor. This will be extended to estimating the cost per quality adjusted life year (QALY) gained using the survival data at 240-day-after enrolment follow-up and modelling the anticipated QALYs gained for these patients based on life expectancy and QALYs gained in ICU survivors in the region.

Statistical analysis will be carried out using the latest version of R.

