This is only the second study of intrathecal antitoxin that has attempted to blind attending doctors from treatment. Study staff are not in any way involved in the care of the patients in the study. Staff delivering the study interventions work in a different department and only come to the ICU to deliver the intervention (in a screened off area). Staff collecting end-point data are also independent from those delivering care and are not employed within the ICU. Mortality rates from tetanus in our unit are low and we have chosen mechanical ventilation as a primary endpoint as this is a clinically important outcome. Not only do patients requiring mechanical ventilation have significantly increased costs, but in our setting they also are central to the transmission of hospital acquired infection and the growing problem of antimicrobial resistance. Despite having ventilation criteria, we feel that this endpoint still may be subject to bias and therefore have designed a blinded study. We have used secondary outcomes of drug use, duration of ventilation and the occurrence autonomic dysfunction as additional markers of disease severity. In addition, we have added health economic analysis. We therefore hope that this trial will provide high-quality evidence for the use of intrathecal antitoxin valuable to all settings.

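### The planned cost-per-survivor ratio sets costs running to day 240 against ICU survivors, an undefined count that is not one of the trial's mortality endpoints

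*Protocol article*

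**What the plan says.** The cost-effectiveness paragraphs of section 5.2 take the healthcare provider's perspective. They count the costs of the intervention in the ICU and the costs of the rest of the hospital stay, "as well as any costs associated with re-admission during the 240 day follow-up".

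Two effect measures follow. The first is conditional: "If the intervention does improve patient survival at a higher cost", then "we will calculate the incremental cost per ICU survivor". The second extends this to a cost per QALY gained, "using the survival data at 240-day-after enrolment follow-up" together with modelled life expectancy.

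Section 2.2 lists mortality as "In hospital and 240-day mortality and disability". Section 5.2 plans Kaplan-Meier curves for 240-day mortality and adds: "Formal comparisons of these outcomes (and in-hospital mortality) will be based on Cox regression models". Neither section lists or analyses mortality at ICU discharge.

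**The concern.** A cost-effectiveness ratio should measure cost and effect over the same period. Here the costs run to day 240, while the effect, read naturally, stops when the patient leaves the ICU. Someone who dies on the ward or during a re-admission adds those later costs and is still counted as a survivor. The next step of the same analysis switches to survival at day 240, so the two ratios would rest on different survivor counts.

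Cost-effectiveness is a stated secondary objective (section 1.2), and a cost per survivor is a figure readers are likely to quote. Its denominator is a difference between two survival proportions. The Discussion says "Mortality rates from tetanus in our unit are low", so that difference is likely to be small, and a few deaths after ICU could move the ratio noticeably.

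**Working it through.** **Time points set side by side**

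| Element | Time point | Where |
|---|---|---|
| Costs | ICU, rest of hospital stay, re-admissions in the 240-day follow-up | 5.2 |
| Trigger for the ratio | better survival, no time point given | 5.2 |
| Effect, first ratio | ICU survivor, not defined | 5.2 |
| Effect, second ratio (QALY) | survival 240 days after enrolment, then modelled | 5.2 |
| Mortality endpoints | in hospital; 240 days | 2.2 |
| Mortality analyses | in hospital; 240 days | 5.2 |

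The first ratio is the only element tied to ICU survival.

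**Size.** The article gives no cost, ICU mortality or post-ICU mortality figure, so there is no planned figure to reproduce. The rates below are assumptions chosen to show a range.

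Let m be ICU mortality and p the mortality between ICU discharge and day 240 among those who left the ICU alive, with subscripts C (no intrathecal treatment) and T (intrathecal treatment).

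- ICU survival gain: D_ICU = m_C − m_T
- 240-day survival gain: D_240 = (1 − m_T)(1 − p_T) − (1 − m_C)(1 − p_C)
- With the same incremental cost to day 240 in both numerators, that cost cancels: (cost per 240-day survivor) / (cost per ICU survivor) = D_ICU / D_240

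| m_C, m_T | p_C, p_T | D_ICU | D_240 | D_ICU / D_240 |
|---|---|---|---|---|
| 10%, 5% | 0, 0 | 0.05 | 0.0500 | 1.00 |
| 10%, 5% | 2%, 2% | 0.05 | 0.0490 | 1.02 |
| 10%, 5% | 5%, 5% | 0.05 | 0.0475 | 1.05 |
| 10%, 5% | 3%, 5% | 0.05 | 0.0295 | 1.69 |
| 10%, 5% | 5%, 3% | 0.05 | 0.0665 | 0.75 |
| 6%, 3% | 0, 0 | 0.03 | 0.0300 | 1.00 |
| 6%, 3% | 2%, 2% | 0.03 | 0.0294 | 1.02 |
| 6%, 3% | 5%, 5% | 0.03 | 0.0285 | 1.05 |
| 6%, 3% | 3%, 5% | 0.03 | 0.0097 | 3.09 |
| 6%, 3% | 5%, 3% | 0.03 | 0.0479 | 0.63 |

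One row in full (6%, 3%; 3%, 5%): D_240 = 0.97 × 0.95 − 0.94 × 0.97 = 0.9215 − 0.9118 = 0.0097, and 0.03 / 0.0097 = 3.09.

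When p is equal in both groups, D_240 = D_ICU × (1 − p), so the factor is 1/(1 − p): 1/0.98 = 1.02 and 1/0.95 = 1.05. A factor above 1 means the ICU-survivor ratio is lower than the 240-day one; a factor below 1 means it is higher.

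**What 2 points means in patients.** The 272 planned patients give 272/2 = 136 in each intrathecal comparison group. With ICU mortality of 3% to 10%, 0.97 × 136 = 132 down to 0.90 × 136 = 122 leave the ICU alive. Two per cent of these is 2.4 to 2.6, so two or three deaths in one group are enough to produce the larger shifts.

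**Start of the 240 days.** The QALY step in section 5.2 counts from enrolment. The Discussion describes follow-up to 240 days after hospital discharge. Section 2 says "Patients will be followed following discharge from hospital until 240 days for disability/ death", which can be read either way. Any fixed horizon inherits this ambiguity.

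**The case against.** The strongest reply is that the article never says the count is taken at ICU discharge. Every participant is an ICU admission (section 3.1), so an ICU survivor could simply be a trial patient who survived, and the next sentence uses the same term as a population label. It is true that ICU discharge is a natural reading and not a stated definition. But the looser reading leaves the measure with no time point, and the trigger supplies none either. Under one reading the periods do not match; under the other the effect is not fixed. The same wording change settles both.

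A second reply is that the time point belongs in a full protocol or health-economic plan. That would hold if the article were silent. It instead names a measure that differs from its own mortality endpoints and from its next step.

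Three stronger conclusions are tempting but not supported:

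- **That the whole cost-effectiveness analysis is affected.** Two ratios are planned, and the cost per QALY already uses 240-day survival.
- **That the ratio is understated.** That needs part of the ICU gain to be lost by day 240. If post-ICU mortality is lower with intrathecal treatment, the ICU-survivor ratio is overstated instead. The documents fix neither direction.
- **That the count could not be checked against the trial's data.** Patients are recorded daily in the ICU (section 3.10), so ICU deaths should be separable from later ones even though ICU mortality is not an endpoint.

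Finally, the ratio is calculated only if survival improves at a higher cost, and so may never be reported. That limits the importance of the point but does not remove it.

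**Conclusion.** The point holds for the cost-per-survivor ratio only. Its costs run to day 240, and its effect is an undefined count that reads most naturally as alive at ICU discharge and matches neither mortality endpoint. On that reading, patients who die after ICU count as survivors with their later costs included.

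The size depends on rates the documents do not give. On the assumed rates the factor is 1 with no post-ICU deaths, 1.02 to 1.05 with equal post-ICU mortality of 2% to 5%, and 0.63 to 3.09 with a 2-point difference between groups. The neutral case is therefore minor and the direction is unknown.

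This is a minor improvement to a conditional secondary analysis. The primary endpoint, the mortality comparisons and the cost per QALY are untouched by the choice of survivor count.

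**What to change.** In section 5.2, replace the cost per ICU survivor with the incremental cost per survivor at 240 days, and count costs and survival over the same 240 days. This matches the cost horizon, a listed endpoint and the QALY step, and needs no new data because 240-day survival is already collected.

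If an ICU-survivor ratio is kept for comparison with other studies, define it as alive at ICU discharge and limit its costs to the ICU stay.

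At the same time, state once whether the 240 days start at enrolment or at hospital discharge, and bring sections 2 and 5.2 and the Discussion into line.

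The cost is a wording change and less direct comparability with published cost-per-ICU-survivor figures; keeping the second, ICU-only ratio recovers that comparability.

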## Discussion

Tetanus is a vaccine preventable disease that remains a significant health problem mainly in remote or low-resource settings with limited access to modern intensive care facilities
^2,
6^. Currently in these settings mortality from tetanus remains high, and simple but effective interventions are very much needed. Due to the ubiquitous nature of
*Clostridium tetani,* the causative organism
*,* complete disease eradication is not possible and unvaccinated populations will continue to contract the disease throughout the word. As even in well-resourced settings, tetanus is associated with high healthcare costs, prolonged ICU stay and long-term disability; effective treatments that can shorten hospital stay and reduce healthcare costs are still needed. We are carrying out this study as we believe intrathecal antitoxin is an intervention with the potential to benefit all patients with tetanus and can be performed in most settings.

This is the first study of intrathecal antitoxin in Vietnam and we have focused on safety at all stages of this study. Prior to embarking on this randomized controlled trial, a pilot study was performed in which 5 patients were treated with open-label human antitoxin intramuscularly and intrathecally. These patients were recruited sequentially and new patients were only enrolled after previous patients were discharged, and clinicians and the trial Data and Safety Monitoring Board were satisfied it was safe to continue. The pilot study results, including all AEs were reported to the trial DSMB, Hospital for Tropical Diseases Ethics Committee and the Ministry of Health Viet Nam Ethics Committee and permission to proceed obtained before enrolment in the randomized controlled trial was commenced. Whilst previous studies have reported reassuringly few AEs associated with administration of intrathecal antitoxin, patients in this study will be followed carefully daily by study physicians and nurses for any evidence of AEs. Furthermore patients will be followed up 240 days after discharge from hospital.

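### The planned cost per QALY names survival as its only trial outcome, so as written a difference between arms in 240-day disability does not enter the QALYs gained

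*Protocol article*

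**What the plan says.** Cost-effectiveness of intrathecal antitoxin is a secondary objective (protocol article, Section 1.2). Section 5.2 sets out the economic analysis in steps.

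- The first ratio is conditional: "If the intervention does improve patient survival at a higher cost, we will calculate the incremental cost per ICU survivor".
- That calculation is then extended to a cost per QALY. The trial's own outcome data enter this step by "using the survival data at 240-day-after enrolment follow-up". The remaining inputs are external, the method being described as "modelling the anticipated QALYs gained for these patients based on life expectancy and QALYs gained in ICU survivors in the region".
- On the cost side, the analysis covers the hospital stay, time on the ventilator and "any costs associated with re-admission during the 240 day follow-up".

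Elsewhere the article plans to collect disability. Section 2.2 lists "In hospital and 240-day mortality and disability" as a secondary endpoint, and Section 2 says: "Patients will be followed following discharge from hospital until 240 days for disability/ death". The Discussion says that "tetanus is associated with high healthcare costs, prolonged ICU stay and long-term disability", and also that "Mortality rates from tetanus in our unit are low".

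**The concern.** The follow-up to day 240 yields two outcomes, death and disability, and the QALY step names only the first. Life expectancy and the quality weights come from outside the trial. Nothing in the named inputs lets the health state of survivors differ by arm.

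A QALY is meant to combine length and quality of life. If intrathecal antitoxin leaves survivors with less disability, the estimate misses part of the gain. If it leaves them with more, for example through neurological harm, the estimate misses the loss. Mortality in this unit is described as low, so the one trial outcome that can move the QALY estimate has limited room to do so. At stake is whether the reported cost per QALY describes the patients in this trial.

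**Working it through.** The article states no QALY figure, so there is nothing to reproduce. The check is an identity, followed by an illustration.

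**Identity.** For arm i (1 = intrathecal, 0 = sham), let S_i be survival, L the life-years per survivor and u_i the mean utility of survivors.

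- QALYs per patient in arm i = S_i × L × u_i.
- With the inputs Section 5.2 names, and one regional value u for both arms, the difference = L × u × (S_1 − S_0). Disability does not appear.
- Setting u at the sham-arm value u_0, the term left out is L × S_1 × (u_1 − u_0). This equals L × S_1 × (reduction in disability risk) × (utility loss from disability).

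**Illustration for the case the plan reaches (survival improves).** None of these values is in the documents; all are assumed:

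- L = 10 undiscounted years, with the disability difference persisting throughout
- utility 0.8 without disability
- disability in 30% of control-arm survivors
- utility loss d from disability of 0.1 to 0.3
- survival 95% (sham) and 97% (intrathecal)
- regional utility equal to the control-arm mean, 0.8 − 0.30d

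Stated method: 10 × (0.8 − 0.30d) × (0.97 − 0.95).

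Full value with disability p in intrathecal survivors: 10 × [0.97 × (0.8 − p × d) − 0.95 × (0.8 − 0.30d)].

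| d | Stated method, any p | Full value, p = 20% | Full value, p = 35% |
|---|---|---|---|
| 0.1 | 10 × 0.77 × 0.02 = 0.154 | 10 × (0.97 × 0.78 − 0.95 × 0.77) = 0.251 | 10 × (0.97 × 0.765 − 0.95 × 0.77) = 0.106 |
| 0.2 | 10 × 0.74 × 0.02 = 0.148 | 10 × (0.97 × 0.76 − 0.95 × 0.74) = 0.342 | 10 × (0.97 × 0.73 − 0.95 × 0.74) = 0.051 |
| 0.3 | 10 × 0.71 × 0.02 = 0.142 | 10 × (0.97 × 0.74 − 0.95 × 0.71) = 0.433 | 10 × (0.97 × 0.695 − 0.95 × 0.71) = −0.004 |

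The omitted term accounts for the gap. At d = 0.1 and p = 20% it is 10 × 0.97 × 0.10 × 0.1 = 0.097, and 0.154 + 0.097 = 0.251.

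For any fixed cost difference, a 10-point reduction in disability makes the stated cost per QALY too high by a factor of 0.251/0.154 = 1.6 to 0.433/0.142 = 3.0. A 5-point increase makes it too low, and at d = 0.3 the apparent gain disappears.

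**Equal survival.** The trigger in Section 5.2 is not met, so no cost per QALY is produced.

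**The case against.** The best reply is that the QALY method takes one sentence of a journal article, and that utility sources and health-state mapping usually sit in a health-economic plan that is not shown. The sentence does not say that disability is left out, nor that a single mean is given to every survivor; regional values could be applied by functional state. This stands as a limit. A reader might infer that the plan deliberately excludes disability, and the text does not support that. But the article does name its inputs, and the only trial outcome among them is survival. If a fuller plan uses disability, the sentence in Section 5.2 needs to say so.

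A reader might also infer that the plan would report zero QALYs gained if disability fell and survival were equal. It would not: the QALY step extends a ratio that is calculated only when survival improves at higher cost.

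Nor do the documents show that a disability effect is the likeliest benefit or harm. They give no disability rate or expected effect. Section 8.3 lists lower mortality among the possible benefits, and reports no serious side-effects in 390 patients from studies that looked for them.

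Finally, disability is a secondary endpoint in its own right, so a difference would be visible beside the economic result, and some of its consequences may enter through readmission costs. Both are true, but neither puts disability into the QALY term.

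**Conclusion.** The point holds in a limited form. With the inputs that Section 5.2 names, the QALY difference between arms reflects survival alone and does not respond to disability among survivors, although the trial follows patients for disability over the same 240 days. Where the plan does calculate the ratio, the error can run in either direction. On the assumed values, the stated method gives 0.14 to 0.15 QALY per patient, against 0.25 to 0.43 with a 10-point disability reduction and about 0.11 down to about 0 with a 5-point increase.

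These figures show the mechanism and do not forecast this trial. They depend on the assumed survival, disability, utilities and horizon, and on reading the regional value as common to both arms. The consequence is confined to a conditional part of a secondary economic objective; the primary analysis is untouched. This is a worthwhile, inexpensive improvement.

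**What to change.** In Section 5.2, add 240-day disability category by randomised arm as an input to survivors' utilities. Use the regional ICU-survivor values to assign a utility to each category and to extrapolate beyond day 240. Report the survival-only model alongside as a sensitivity analysis.

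The cost is some extra modelling on outcome data that are already to be collected. The drawback is that the article does not describe the disability scale, so the mapping from category to utility has to be assumed. State that mapping in advance and vary it over a stated range.
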